### **10.3.24 Blood tests**

No blood testing is required under this protocol. The results of any blood testing (including the dementia blood workup performed before participation in this study) that is performed for participants during this study will be recorded in the eCRF.

### **10.3.25 Optional neuropsychological testing**

During this study, participants may undergo neuropsychological testing that is not required under this protocol. The results of any such testing will be recorded in the eCRF.

#### **10.3.26 Other data**

Other data that is collected from the participants during this study may be recorded in the eCRF.

### **10.4 Appropriateness of Measurements**

All clinical assessments and measurements are appropriate and generally regarded as standard medical practice.

## **11 DATA HANDLING AND QUALITY ASSURANCE**

### **11.1 Data Recording**

Data required per this protocol are to be entered into the eCRFs (provided by the Sponsor) as soon as possible; it is expected that will be within 5 days after the information becomes available.

### **11.2 Electronic Case Report Forms**

eCRFs will be used for collecting all data generated during the study, including the diagnostic findings from the PET read.

All data found in the eCRF will be transcribed from source documentation maintained by the Principal Investigator or designee. All data will be entered into the eCRF by trained site personnel, with reasons given for any missing data. Any errors should be corrected within the electronic system. The audit trail will record all changes made, the date and time of the correction, and the person correcting the error.

### **11.3 Clinical Data Management**

The Sponsor or a qualified delegate (ie, a contract research organization [CRO]) will be responsible for the processing and quality control of the data. Data management will be carried out by the Sponsor or CRO. The handling of data, including data quality control, will comply with all applicable regulatory guidelines.

### **11.4 Data Processing**

Study data documentation will be maintained specifying all relevant aspects of data processing for the study (including data validation, cleaning, correcting, releasing). This documentation will be stored in the Trial Master File (TMF).

For data coding, internationally recognised and accepted dictionaries will be used. These and the processes used for coding will be specified in the SAP.

### **11.5 Archiving**

Essential documents will be archived safely and securely in such a way that ensures that they are readily available upon Regulatory Authorities' request. Clinical study documentation must be maintained for at least 15 years after the end of the study or its anticipated stop, or longer if this is anticipated by a contract between the Sponsor and investigator.

The investigator/institution must notify the Sponsor if the archival arrangements change (e.g., relocation or transfer of ownership).

The investigator site file is not to be destroyed without the approval of the Sponsor.

## **11.6 Data Pseudonymization**

Data on the eCRF will be coded and each patient will be identified by PID (see Section 8.3.1).

A patient log (i.e a file that includes the correspondence between the PID and patients' name and Date of Birth) will be maintained for all the duration of the study, and for at least 15 years after the end of the study, as specified in national legal regulations.

The access to and the maintenance of this file will be under the responsibility of the PI.

## 12 STATISTICAL METHODS AND PLANNED ANALYSIS

The data will be analysed by the Sponsor and/or designated CRO. Any data analysis carried out independently by the investigator should be submitted to the Sponsor before publication or presentation.

Data from participating centres in this protocol will be combined so that an adequate number of participants will be available for analysis. The data will be summarised with respect to demographic and baseline characteristics, efficacy observations and measurements, and safety observations and measurements.

### 12.1 General Statistical Considerations

A separate Statistical Analysis Plan (SAP) will be prepared before the start of the statistical analysis to provide further details on the statistical analysis and formalise data outputs from this clinical study.

Tabulations of summary statistics, graphical presentations, and statistical analyses will be performed with SAS® software, Version 9.2 or higher. Descriptive statistics for continuous data in summary tables will include the number of participants in the analysis (n), mean, standard deviation, median, and range (minimum, maximum). Descriptive statistics for categorical data in summary tables will include counts and percentages.

All data obtained on the eCRF and entered into the database will be provided in separate data listings showing individual participant values. All summary tables and data listings will be separated by treatment groups. The planning and reporting of statistical analysis will be carried out as described in the Sponsor or CRO's standard operating procedures (SOPs) governing clinical studies.

### 12.2 Populations for Analysis

**Safety Analysis Set (SAS):** All participants receiving any amount of either [F]florbetaben or [F]flutemetamol are included in the SAS.

**Full Analysis Set (FAS):** All participants randomized to the Early Amyloid PET, Late Amyloid PET, or Free Choice arm.

**Per Protocol Set (PPS):** All participants randomized to the Early Amyloid PET, Late Amyloid PET, or Free Choice arm with no major protocol deviations that would make them ineligible for the primary efficacy variable. Participants who are lost to follow-up will be excluded from the PPS.

The primary efficacy analysis will be based on the PPS population, and the secondary efficacy analysis will be based on the FAS population.

## **12.3 Participant Demographics/Other Baseline Characteristics**

A table will be provided with the following information:

- Number of participants enrolled.
- Number of participants included in the Full Analysis Set (FAS).
- Number of participants included in the Safety Analysis Set (SAS)
- Number of participants included in the Per Protocol Set (PPS)
- Number of participants withdrawn from the study and the reason for withdrawal.

For SAS, FAS, and PPS, demographic information (age, height, weight, and body mass index) will be summarised with descriptive statistics. Gender and race will be summarised by counts and percentages. Medical histories will be summarised by counts and percentages. Concurrent medications will be recorded and coded by using a standard classification system and grouped by primary and secondary classes, if applicable. The primary efficacy analysis will be based on the PPS population, and the secondary efficacy analysis will be based on the FAS population.

### **12.3.1 Physical examination findings**

A physical examination will be performed during screening.

### **12.3.2 Vital signs**

Vital signs will be recorded at screening.

## **12.4 Study Treatments**

## **12.5 Primary Analysis**

### **12.5.1 Primary Efficacy Variables**

The primary variable will be the difference, at 12 weeks after baseline, between the Early Amyloid PET arm and the Late Amyloid PET arm in the proportion of patients for whom the managing physician has made an etiologic diagnosis with very high confidence ( $\geq 90\%$ ).

Diagnostic confidence, which is the managing physician's confidence that the diagnosis is correct, will be measured with a visual analogue scale (VAS) from 0% (no confidence) to 100% (full confidence).

### **12.5.2 Statistical hypothesis, model, and method of analysis**

The difference between the Early Amyloid PET and Late Amyloid PET arms in the proportion of patients with an etiologic diagnosis in which the managing physician has  $\geq 90\%$  confidence at 12 weeks (the primary endpoint) will be evaluated with a chi-squared test with significance level of .05.

For each of the three strata (SCD Plus, MCI, and dementia) separately, the difference between the Early Amyloid PET arm and the Late Amyloid PET arm in the proportion of patients with an etiologic diagnosis with a confidence  $\geq 90\%$  at 12 weeks will be evaluated with a chi-squared test with an overall significance level of .05. The Bonferroni correction will be applied to control the family-wise type I error rate.

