### 8.3.2 Randomisation

This is a phase 4, open label, randomised study.

Patients will be randomised in a 1:1:1 ratio into 1 of the following 3 groups:

- **Early Amyloid PET arm:** These participants will undergo amyloid PET imaging within 4 weeks after baseline. The results of the PET imaging must be communicated to the managing physician as soon as they are available. Amyloid PET will be carried out with high priority for early amyloid PET arm patients. For participants in this arm, an optional second amyloid PET scan will be performed 12 to 18 months ( $\pm 28$  days) after the initial scan.
- **Late Amyloid PET arm:** These patients will undergo amyloid PET imaging at 8 months  $\pm 8$  weeks after baseline.
- **Free Choice arm:** The managing physician will choose whether and when each participant will have amyloid PET imaging at any time between baseline and 12 months after baseline.

Randomization will be performed by using permuted blocks assuring equal numbers to all arms. Randomization will be stratified by centre and baseline syndromic diagnosis. Participants will be randomly assigned (1:1:1) to 1 of 3 arms and randomization will continue until 300 SCD plus, 300 MCI, and 300 dementia where AD is a differential diagnosis have been included.

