## **12.6 Secondary Analyses**

### **12.6.1 Secondary efficacy variables**

In the analyses of the secondary efficacy variables, a cross-sectional difference between arms in a secondary endpoint at T1, T2, T3, or T4 (see Table 1) will be carried out by a chi-squared test if the endpoint is dichotomous, a 2-sided *t*-test if the endpoint is normal, and Mann-Whitney test if the endpoint is categorical or continuous and non-normal. The effect of baseline characteristics such as age, gender, MMSE, etc will be studied by a linear or logistic regression model.

A difference between study arms in the longitudinal change of a secondary endpoint will be tested by means of logistic or linear regression where the first measurement is a covariate (ANCOVA analysis) and the second measurement is the outcome. Differences in longitudinal

trends between arms will also be examined by means of the mixed-effects regression model. The effects of baseline characteristics such as age, gender, MMSE, etc. will be studied by including them in the regression models.

All tests will be 2-sided and the significance level will be set at 5%. Bonferroni corrections for multiple testing will be applied when appropriate. Point estimates will be presented together with 95% Wald confidence intervals. A 95% non-parametric confidence interval will be constructed if the estimate is non-normal.

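### Randomisation is stratified by centre and syndromic diagnosis, but the overall primary test is an unstratified chi-squared test; if outcome rates differ between strata, it is conservative and gives up some power

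*Protocol*

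**What the plan says.** Section 8.3.2 (Randomisation) states: "Randomization will be stratified by centre and baseline syndromic diagnosis". It also states: "Randomization will be performed by using permuted blocks assuring equal numbers to all arms". Recruitment continues until each of the three diagnoses (SCD-plus, MCI, dementia) has 300 patients.

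Section 12.5.2 and the synopsis fix the analysis of the primary endpoint, which is an etiologic diagnosis held with at least 90% confidence at 12 weeks. The difference between the Early and Late arms "will be evaluated with a chi-squared test with significance level of .05". No stratification factor or covariate is named. A second paragraph adds a chi-squared test within each diagnosis, for which "The Bonferroni correction will be applied to control the family-wise type I error rate".

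Centre enters only in section 12.5.4, through a Breslow-Day test of homogeneity, with centre-specific effects if the test indicates variation. Section 12.7 gives the power of the overall test at differences of 25, 20, 15 and 10 points as more than 99%, 99.6%, 93% and 61%, and the power of each stratum test at 25 points as 80%.

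**The concern.** Stratified permuted blocks keep the arms balanced within each diagnosis and centre. Differences in outcome rate between strata therefore contribute almost nothing to the sampling error of the Early-minus-Late difference. A pooled chi-squared test estimates its variance from the overall rate, so it counts those differences as error. Its standard error is then too large, its p-value too high and the matching confidence interval too wide.

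The other planned analyses do not repair this. The stratum tests condition on diagnosis but yield three separate answers, each at a reduced significance level, and they ignore centre. The Breslow-Day test asks whether centre-specific odds ratios agree; it estimates no common effect. What is at stake is a modest but real effect missed with the same patients.

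**Working it through.** **Inputs from the protocol.** 300 per arm with 10% withdrawal gives n = 270 evaluable per arm (section 12.7), or 90 per arm in each of three equal strata (section 8.3.2). The significance level is 0.05, taken as two-sided from section 12.6.1, which words that rule as covering all tests.

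**Assumed.** All outcome rates, because the protocol gives none, and equal withdrawal across strata.

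**Step 1: reproduce the protocol's power.** For Late and Early rates p1 and p2, with d = p2 − p1 and p̄ their mean:

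power = Φ[(d − 1/n − 1.96·se0)/se1], where se0 = √(2p̄(1−p̄)/n) and se1 = √((p1(1−p1) + p2(1−p2))/n).

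With rates centred on 50% and d = 0.10, se0 = 0.0430 and se1 = 0.0428. Then (0.10 − 0.0037 − 0.0843)/0.0428 = 0.28, so power is 61.0%. At 15, 20 and 25 points the formula gives 92.7%, 99.6% and 99.99%. A stratum test with n = 90, α = 0.05/3 and d = 0.25 gives 79.9%. All the stated figures reproduce, so they belong to an unstratified two-proportion test with continuity correction. Without the correction the 10-point figure is 64.3%. The results below use no correction and should not be set against the protocol's 61%.

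**Step 2: true level of the pooled test.** Let p_k be the rate in diagnosis k under no effect, W the mean of p_k(1−p_k), and p̄ now the mean of the p_k. The true variance of the difference is 2W/n; the pooled test uses 2p̄(1−p̄)/n. With r = W/[p̄(1−p̄)], the true level is 2[1 − Φ(1.96/√r)].

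Example, 10/35/65%: W = (0.09 + 0.2275 + 0.2275)/3 = 0.1817 and p̄(1−p̄) = 0.3667 × 0.6333 = 0.2322. So r = 0.782, 1.96/√r = 2.216, and the true level is 2.7%.

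**Step 3: power.** Add d to each Late-arm rate. Power is Φ[(d − 1.96·se)/se1]. Here se1 uses within-stratum variances for both tests. The pooled test takes se from the overall midpoint rate; the stratified test takes it from the mean within-stratum variance at the stratum midpoints.

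Same example, d = 0.10: pooled se = √(2 × 0.2431/270) = 0.0424; stratified se = √(2 × 0.1925/270) = 0.0378; se1 = √((0.1817 + 0.1983)/270) = 0.0375. Power is 67.3% pooled and 75.6% stratified.

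| Assumed Late-arm rates, SCD-plus/MCI/dementia | True level, pooled | 10 points: pooled → stratified | 15 points | 25 points |
|---|---|---|---|---|
| 50/50/50% | 5.0% | 64.7 → 64.7% | 94.3 → 94.3% | about 100% both |
| 40/50/60% | 4.7% | 64.9 → 65.9% | 94.6 → 94.9% | about 100% both |
| 20/35/50% | 4.3% | 66.6 → 68.9% | 94.9 → 95.5% | about 100% both |
| 10/35/65% | 2.7% | 67.3 → 75.6% | 96.1 → 97.8% | about 100% both |
| 5/30/70% | 1.8% | 69.0 → 81.0% | 97.1 → 98.8% | about 100% both |

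A simulation of 300,000 trials per cell for the last three rows agreed within half a point on power. It put the level of the Cochran-Mantel-Haenszel test at 4.9 to 5.0%.

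**Step 4: centre.** A further simulation assumed nine equal centres, two-arm average rates of 30/50/70% and a between-centre SD of 1 on the logit scale. The pooled level was 3.0%. Power at 10 points rose from 67.1% to 75.8% when stratifying by diagnosis and centre.

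**Step 5: baseline confidence, a separate mechanism.** With a binary baseline predictor shifting the logit by ±1, the level of the chi-squared test stayed at about 5%. Power at 10 points rose from 65.5% to 75.0% when the predictor was used. Leaving it out costs power but does not make the test conservative, because it is not a randomisation stratum.

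**The case against.** The strongest objection is that the loss is conditional and immaterial where the trial was sized. The protocol gives no rates. With equal rates nothing is lost, and with mild separation (40/50/60%) the gain is one point. At the planned 25 points both tests have about 100% power, and at 15 points the gain is at most about two. All of that stands. It limits the size of the point, but it gives no reason to drop the design factors from the overall test.

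Four stronger readings are tempting, and the documents do not support them:

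- **That the primary test is invalid.** Its level is at or below 5%, so a significant result remains trustworthy.
- **That ignoring baseline confidence makes the test conservative.** It does not (step 5).
- **That the protocol treats the primary endpoint less carefully than the secondary ones.** Section 12.6.1 adjusts for the first measurement only when longitudinal change is analysed. For a dichotomous endpoint at one timepoint it also specifies a plain chi-squared test, with baseline characteristics studied separately by regression.
- **That baseline confidence can simply be added to the model.** Section 9.2 records confidence for up to four etiologic hypotheses, and section 6.1.1 describes baseline confidence in the syndromic diagnosis. A single number must be defined first.

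**Conclusion.** The mismatch is real and fixed in the protocol text: the design stratifies by centre and diagnosis, and the overall primary test uses neither. The consequence is conditional. Under the assumed rates, and counting diagnosis alone, the pooled test runs at about 1.8 to 5.0% instead of 5%. Stratifying by diagnosis gains 0 to about 12 points of power at a 10-point difference, about 0 to 2 at 15 and none at 25. If centres also differ, stratifying by centre can add to the gain. These figures rest on 90 evaluable patients per arm per stratum and on rates that the protocol does not supply. This is a worthwhile efficiency and consistency correction, and it does not call the trial's validity or its planned power into question.

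**What to change.** In section 12.5.2 and the synopsis, make the overall primary test a Cochran-Mantel-Haenszel test stratified by syndromic diagnosis and centre, pooling small centres by a rule fixed before database lock. Report a stratified risk difference with its 95% confidence interval. Keep the unstratified chi-squared test as a sensitivity analysis, and leave the Bonferroni-corrected stratum tests and the Breslow-Day test as planned. While editing, align the synopsis and section 6.1.1, which name only diagnosis as a stratification factor, with section 8.3.2.

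Optionally, and for power only, fit a logistic model that adds T0 diagnostic confidence and report a standardised risk difference. Define the covariate first as one number, for example the highest confidence among the etiologic hypotheses recorded at T0 before randomisation.

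The cost is protocol and SAP wording. No new data are needed.

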##### **Primary Efficacy Analysis**

- The difference between the Early Amyloid PET and Late Amyloid PET arms in the proportion of patients with an etiologic diagnosis in which the managing physician has  $\geq 90\%$  confidence at 12 weeks (the primary endpoint) will be evaluated with a chi-squared test with significance level of .05.
- For each of the three strata (SCD Plus, MCI, and dementia) separately, the difference between the Early Amyloid PET arm and the Late Amyloid PET arm in the proportion of patients with an etiologic diagnosis with a confidence  $\geq 90\%$  at 12 weeks will be evaluated with a chi-squared test with overall significance level of .05. The Bonferroni correction will be applied to control the family-wise type I error rate.
- Heterogeneity with respect to the effect on the primary variable between centres will be evaluated with the Breslow-Day test of homogeneity. If this effect varies across centres, centre-specific effects will be calculated.

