## **12.7 Sample Size Calculation**

For the primary efficacy analysis, a sample size of 300 per arm yields more than 99% power when a difference in proportion of 25% is assumed and 10% of the participants are assumed to withdraw before the end-point is reached. For difference in proportion of values of 20%, 15%, and 10%, the power is 99.6%, 93%, and 61%, respectively. For each of the three strata (SCD Plus, MCI, and dementia), a stratum sample size of 100 per arm yields 80% power when the difference is 25% and 10% of the patients withdraw before the end-point is reached.

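### Holm in place of single-step Bonferroni for the three stratum tests keeps the same 5% control and returns stratum power; the 5% should also be said to cover the stratum set only

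*Protocol*

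**What the plan says.** - Section 12.5.1 names one primary variable: "The primary variable will be the difference, at 12 weeks after baseline, between the Early Amyloid PET arm and the Late Amyloid PET arm".
- Section 12.5.2 tests it first; the sentence ends "the primary endpoint) will be evaluated with a chi-squared test with significance level of .05".
- The same section, and the synopsis under Primary Efficacy Analysis, then compare Early with Late in each stratum. Each comparison "will be evaluated with a chi-squared test with an overall significance level of .05", followed by "The Bonferroni correction will be applied to control the family-wise type I error rate".
- Section 12.7 gives the strata their own power statement: "a stratum sample size of 100 per arm yields 80% power when the difference is 25" points, with 10% withdrawal. For the whole trial, "a sample size of 300 per arm yields more than 99% power when a difference in proportion of 25% is assumed".
- Section 12.5.4 (Supportive analyses) holds only the check for heterogeneity between centres.

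No order, gate or alpha split connects the overall test with the stratum tests.

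**The concern.** Section 4.1.1 says that the study is to determine for whom amyloid PET is appropriate, and section 8.3.2 recruits until each stratum holds 300 patients. The stratum comparisons therefore matter, and they are where power is tight: at the planned effect the overall test has more than 99% and each stratum 80%. Single-step Bonferroni holds every stratum to 0.05/3 even after another stratum has been rejected, which is stricter than 5% family-wise control requires. The price is stratum findings missed on the same data.

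Separately, a reader cannot tell from the text what standing a significant stratum has when the overall test fails.

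**Working it through.** **1. Reproduce the plan's power.** Inputs from 12.7: 300 per arm overall and 100 per arm per stratum, less 10%, so n = 270 and n = 90. The protocol gives no base rates, so I assume rates centred on 50%. For a two-sided chi-squared test with continuity correction:

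power = Φ[(Δ − 1/n − z·√(0.5/n)) / √((p1q1 + p2q2)/n)]

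For a stratum, Δ = 0.25 (0.375 against 0.625), n = 90 and z = 2.394 at 0.05/3:

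(0.25 − 0.0111 − 2.394 × 0.0745) / 0.0722 = 0.838, so power = 79.9% (stated: 80%).

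Overall, at 20, 15 and 10 points, the formula gives 99.6%, 92.7% and 61.0% (stated: 99.6%, 93%, 61%). Without the correction the 10-point figure is 64.3% and the stratum figure 83.9%, which do not match. With the correction, stratum power would be about 77% at 0.05/4 and 90.1% at 0.05. So the stated 80% was computed at 0.05/3, and the overall test was not counted in the Bonferroni family.

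**2. Holm's rule.** Order the three p-values. Compare the smallest with 0.05/3, the next with 0.025 and the largest with 0.05, and stop at the first failure. The first step is the Bonferroni test, so whatever Bonferroni rejects Holm rejects too.

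**3. Power with all three strata at the planned effect.** Set the mean of each stratum Z so that power at 0.05/3 is 80%: 2.394 + 0.842 = 3.236. Then:

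- P(p < 0.05/3) = 0.800
- P(p < 0.025) = Φ(3.236 − 2.241) = 0.840
- P(p < 0.05) = Φ(3.236 − 1.960) = 0.899

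The band between 0.05/3 and 0.025 has probability 0.040, and the band between 0.025 and 0.05 has 0.059.

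One stratum is rejected by Holm if:

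- its p is below 0.05/3: 0.800; or
- it is in the first band and another stratum is below 0.05/3: 0.040 × (1 − 0.2²) = 0.038; or
- it is in the second band, both others are below 0.025 and at least one of them is below 0.05/3: 0.059 × (0.840² − 0.040²) = 0.042.

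The total is 0.880, against 0.800 under Bonferroni.

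All three significant: Bonferroni 0.8³ = 0.512. Holm 0.840³ + 3 × 0.059 × 0.840² = 0.717; removing the cases with no p below 0.05/3 takes off less than 0.001. That is about 72%.

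**4. Check by binomial simulation** (n = 90, 0.375 against 0.625):

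| Test | Per stratum, Bonferroni → Holm | All three, Bonferroni → Holm |
|---|---|---|
| With continuity correction | 79.0% → 87.2% | 49.2% → 70.0% |
| Without | 83.3% → 90.5% | 57.9% → 76.5% |

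**5. Fewer strata with an effect.**

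- Two strata: 0.800 + 0.040 × (1 − 0.2 × 0.983) + 0.059 × (0.840 × 0.025 − 0.040 × 0.0083) = 0.833, a gain of about 3 points.
- One stratum: 0.800 + 0.040 × (1 − 0.983²) = 0.801, almost no gain.

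In the two-stratum case the false-positive rate in the third stratum rises from 1.7% to 4.6% (uncorrected test), still within 5%.

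**6. The overall and stratum tests read as one family.** The stratum set alone has error 1 − (1 − 0.05/3)³ = 4.92%. With equal strata, Z_overall = (Z1 + Z2 + Z3)/√3. Integrating over the three stratum Z values gives 8.35% for at least one rejection among the four tests when no stratum has an effect. The overall test is unstratified and turns conservative when base rates differ between strata:

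| Base rates (SCD-plus, MCI, dementia; assumed) | Uncorrected | Continuity-corrected |
|---|---|---|
| Equal (0.4) | 8.5% | 6.3% |
| 0.2, 0.4, 0.6 | 7.5% | 5.3% |
| 0.1, 0.4, 0.7 | 6.2% | 4.0% |

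Holm does not change these figures, because under the global null its first rejection occurs exactly when Bonferroni's does.

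**7. Gating the strata on the overall test.** This brings the pooled error to 5%. With all three strata at the planned effect it costs nothing, since overall power exceeds 99.9%. With an effect in one stratum only, the mean of the overall Z is 3.236/√3 = 1.868 and overall power is Φ(1.868 − 1.960) = 46%. That stratum's power then falls from about 80% to 43% (83.3% to 47.6% in the uncorrected binomial simulation).

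**The case against.** **Bonferroni is not an error.** It is valid, it is stated, and the 80% rests on it. That stands: this is an improvement at no cost in error control, not the correction of a fault. The 8-point gain is also the best case and shrinks as effects become confined to fewer strata. That stands too, but Holm never does worse than Bonferroni.

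**Bonferroni has simple matching simultaneous intervals; Holm does not.** True, but the only interval rule stated is 95% Wald intervals, in 12.6.1 for the secondary analyses. No Bonferroni-adjusted interval is planned that would be lost.

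**A stronger reading.** A reader might infer that the protocol claims 5% control over all its primary tests and breaches it at about 8.3%. The text does not support this. The family-wise sentence closes the stratum paragraph and is true of those three tests (4.92%). Objective, endpoint and variable are each defined once, as the overall Early against Late difference, and 12.5.2 attaches the primary label to the overall test alone. The excess arises only if the two sets are pooled, and its size depends on base rates that the protocol does not give. What remains is unclear status: the stratum tests sit under the primary heading and not among the supportive analyses.

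**A statistical analysis plan may set the order of testing.** It may, but the protocol itself names the correction, so the change belongs there as well.

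**Conclusion.** Holm should replace single-step Bonferroni in the stratum set. Family-wise control over the three strata stays at 5%. If all three strata have the planned 25-point effect, power per stratum rises from about 80% to 88% and the chance of three significant strata from about 51% to 72%. This rests on independent strata, 90 evaluable per arm in each, and rates near 50%.

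The secondary point is one of wording. The stated control holds for the three stratum tests. If they and the overall test are read as one primary family, the error under the global null is about 6% to 8.4% with an uncorrected test, depending on how far base rates differ between strata. It is lower with a continuity-corrected test. The error of the overall test taken alone does not exceed its 5%.

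**What to change.** - In 12.5.2 and the synopsis, replace the Bonferroni correction by Holm's procedure for the three stratum tests, at a family-wise 5%.
- In 12.7 and the synopsis, restate stratum power as 80% at the first Holm step and about 88% marginally if all three strata have the planned effect.
- Add one sentence: the overall comparison is the sole primary test, and the 5% family-wise control covers the stratum set only.

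This costs a few sentences, with no new data and no extra patients.

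If the sponsor wants one 5% error over all four tests, gating the strata on the overall test or splitting alpha would do it. Neither is required. The gate is free when all strata benefit but nearly halves a stratum's power when it alone benefits; the choice should rest on how plausible that case is.
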